**Figure 2 F2:**
[figure not shown]
**Illustration of intervention components and desired impact on prescribing behavior**.

Intervention component one: Informatics tool

The informatics tool is central to the intervention, and will involve the extraction of existing GP clinical data to an NHS Tayside database accessible to the DQIP informatics tool developed by Aridhia (an IT company contracted by NHS Tayside for this purpose). The informatics component will:

1. Summarise numbers of patients affected by high-risk prescribing at practice level based on nine validated measures and one composite measure (see outcome measures). This will allow each practice to monitor trends in high-risk prescribing before and after the start of the DQIP intervention.

2. Identify patients affected by high-risk prescribing for review by the practice, and allow practices to select which patients to target first (e.g., patients triggering particular measures, patients triggering multiple measures).

3. Structure clinical information to facilitate review. All decisions about prescribing and organisation of work around DQIP remain a practice responsibility, including deciding which professional is most suited to do any initial record-based review and any follow-up telephone or face-to-face review.

4. Record review decisions using structured data that supports re-identification of patients if necessary, and to measure trial processes for evaluation.

5. Support reminders to practices to review their data via e-mail reminders.

6. Support the educational intervention (provide general information/summaries of the evidence of risk, links to more detailed reference information, prevalence measurement, and run charts for each practice).

The DQIP informatics tool will additionally collect data for trial process evaluation and record data to trigger practice payment at the end of the trial.

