The data held in the NHS Tayside database will be identifiable, and access to it will be controlled in the same way that NHS Tayside controls access to all patient identifiable data (e.g., in Central Vision and other web-based patient information systems), with individual user accounts created at the request of each practice. In NHS Tayside, access will be controlled using the standard lightweight directory access protocol (LDAP) account that primary care clinicians use to access all NHS Tayside clinical databases and tools. In NHS Fife, users will receive a Tayside LDAP guest account with access exclusively granted to the DQIP informatics tool (the exception will be practices in North East Fife which use the Ninewells laboratory and already have Tayside LDAP accounts for Central Vision access). Only practice-based users will have access to identifiable patient information in the informatics tool. For DQIP purposes, a practice-based user is defined as a professional that the practice nominates as an appropriate user, and is expected to include GPs, the practice manager, and (in some cases) primary care pharmacists (who are not practice employees, but often work clinically in practices). With practice permission, the research team will have access to aggregate practice data (prevalence and run charts) during the trial for trial management purposes, and to anonymised patient level data after the trial ends for analysis.

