### Blinding

Due to the nature of the intervention, it is not possible to blind either practices or the core research team (TD, AG, and BG). However, outcome assessment is entirely objective and automated. It is also not possible to blind the analyst because the analysis is a time series in which every practice receives the intervention rather than a comparison between groups. The main analysis will therefore be pre-specified rather than blinded, and any analysis not pre-specified will be clearly identified as such and therefore hypothesis generating/exploratory rather than hypothesis testing/explanatory.

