### Data collection

#### Prescribing outcomes (PO - 1 to 9)

The primary outcome and prescribing secondary outcomes will be measured in each practice at eight weekly intervals (reflecting that the measure numerators are all for high-risk prescriptions in the last eight weeks). At the time of initial data extraction, eight weekly measures will be constructed for the 48 weeks before the intervention start date.

All outcomes will be measured in the informatics tool using identifiable patient data, but only practices will be able to view identifiable data which will remain in an NHS Tayside controlled database. Access to identifiable data will require explicit practice consent for each individual using the tool, and will be controlled by the NHS Tayside LDAP system used for all clinical systems.

During the study, the core research team will be able to view aggregate practice data (run charts of change over time for each measure) and a summary of practice activity (log-ins, reviews, actions taken). At the end of the trial, fully anonymised data will be extracted from the informatics tool database held by NHS Tayside, and transmitted to the research team using established University of Dundee Health Informatics Centre (HIC) Standard Operating Procedures (SOPs) that require robust anonymisation, transmission using appropriate secure encryption, storage of data on securely encrypted computers, and compliance with Data Protection Act regulations.

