### Patient level analysis

The analysis above will be repeated including patient level as well as practice level data. This will be the primary analysis. At the patient level, the primary outcome is binary (yes, no), and so mixed models with binary outcomes will be utilised, i.e., non-linear mixed models. These incorporate the correlation of patients within practices and of repeated measurements over time. At the patient level, descriptive measures will be tabulated such as age, gender, deprivation decile of Scottish Index of Multiple Deprivation (SIMD), number of measures that are relevant to a patient (i.e., the patient meets the denominator definition), as well as the primary and secondary outcomes as percentages.

The mixed model will incorporate fixed terms for intervention (before versus. after), time (eight-week time periods) as well as the correlation of patients within practices and the correlation of repeated measurements over time as random effects. Hence, the analysis will have the element of time series analyses with multiple time points before and after intervention. The primary null hypothesis is no difference in the composite before compared to after intervention as a binary factor. Because patients can be in more than one time period and move in and out of numerators and denominators, the correlation of repeated measures for these individuals will be taken into account in the multilevel modelling. Patients are nested within practices but can be cross-classified with respect to time periods. Initially, this cross classification will be ignored and then the analyses will be repeated with cross-classification terms to assess any differences. These analyses will be repeated for all secondary outcomes.

A formal statistical analysis plan will be documented prior to data lock, and this will form the detailed protocol for analysis. All analyses will be carried out using SAS 9.2 and SPSS v18.

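### Pre-specification stands in for analyst blinding, but the analysis plan is due only by data lock, after before/after run charts have been open to the team throughout the trial

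*Protocol article*

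**What the plan says.** The Blinding section gives the reason for the approach, "It is also not possible to blind the analyst because the analysis is a time series in which every practice receives the intervention", and then the substitute: "The main analysis will therefore be pre-specified rather than blinded". The same section says that analyses not specified in advance will be labelled exploratory. It also notes that "outcome assessment is entirely objective and automated".

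Under Statistical methods, the Patient level analysis section sets the timing of the detailed plan: "A formal statistical analysis plan will be documented prior to data lock". It adds that this plan will govern the analysis in detail. No earlier milestone is given.

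Two sections give access to accumulating outcomes. The account of the informatics tool says that, with practice permission, "the research team will have access to aggregate practice data (prevalence and run charts) during the trial for trial management purposes". The Data collection section on prescribing outcomes says: "During the study, the core research team will be able to view aggregate practice data (run charts of change over time for each measure", alongside a summary of practice activity. On what the tool displays, the account of its first function says: "This will allow each practice to monitor trends in high-risk prescribing before and after the start of the DQIP intervention". Anonymised patient-level data reach the team only after the trial ends.

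The Patient level analysis section states the primary null hypothesis as no before/after difference in the composite, with intervention as a binary factor.

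**The concern.** A deadline of data lock works when outcomes by allocation stay hidden until lock: whoever writes the plan cannot know which choice favours the result. Here a practice's intervention status is known to everyone from its start date, and its outcome trend is on screen. A plan signed just before lock would meet the stated deadline even if every aggregate trend had already been examined.

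Automated outcome assessment does not help, because it protects measurement and not the choice of model. For analytic choices, pre-specification is the only safeguard the article names, so its timing matters. At stake is whether the details settled late can be called pre-specified in the sense the Blinding section intends.

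The point concerns a deadline that the article states. It is not a complaint that details normally left to an analysis plan are absent from the article.

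**Working it through.** The plan states no figure on this point, so there is none to reproduce. The check has two parts: how much outcome information could be seen before the deadline, and which choices remain open to be influenced by it.

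**1. Exposure before the deadline**

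Inputs:
- ten start dates, four weeks apart (Trial design)
- 48 weeks of intervention, measured every eight weeks (Figure 1 legend)
- four practices per start date if forty are recruited (Randomisation and allocation concealment)
- planned gaps around Christmas/New Year and March, of unstated length, set to zero here

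Last start: (10 − 1) × 4 = week 36. Last follow-up: 36 + 48 = week 84. The gaps can only lengthen this.

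Post-start periods per practice: 48 / 8 = 6. Total: 40 × 6 = 240 practice-periods.

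Completed post-start practice-periods at week T are 4 × Σ min(6, ⌊(T − s)/8⌋), summed over start weeks s = 0, 4, …, 36 with s ≤ T:

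| Week | Sum over start dates | Practice-periods | Share of 240 |
|---|---|---|---|
| 0 | 0 | 0 | 0% |
| 24 | 9 | 36 | 15% |
| 36 | 20 | 80 | 33% |
| 48 | 35 | 140 | 58% |
| 60 | 48 | 192 | 80% |
| 84 | 60 | 240 | 100% |

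A plan dated before the first start is written with 0 of 240 visible. A plan dated just before lock may be written with 240 of 240 visible in aggregate.

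Viewing is also built into the schedule. Table 8 has practices receive reports on changes in their prescribing at weeks 8, 16, 24, 32 and 40, and someone has to prepare them.

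**2. What is fixed and what is open**

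Fixed in the article: the composite outcome, the patient-level analysis as primary, a mixed model for a binary outcome, fixed terms for intervention and for time in eight-week periods, random effects for clustering and repeated measurement, and the null hypothesis.

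Left open:

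- *Coding and scale of time.* Outcome periods are built backwards and forwards from each practice's own start, while starts are staggered by four weeks. The article does not say whether the time term is calendar time or time relative to start, nor whether it is categorical or a trend. These are different models. Calendar periods give a stepped-wedge adjustment for secular change. A linear trend in practice-relative time gives an interrupted-time-series contrast. Categorical practice-relative periods cannot be combined with a before/after term at all, because the after indicator equals the sum of the six post-start period indicators. Run charts show the trends that would bear on this choice.
- *Cross-classification.* The model is fitted first without these terms and then with them, and neither fit is named as primary.
- *Baseline adjustment.* The Practice level analysis section says the models are able to include it, without saying that they will or naming covariates. The patient-level analysis is described as repeating that analysis with patient data added, so the option carries over.

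**The case against.** The strongest reply is that the published article is itself the pre-specification and the analysis plan only adds detail. Much of this stands. The core of the primary analysis is public and could not be changed quietly, and the Blinding section already commits to labelling unplanned analyses as exploratory. The cross-classification wording can also be read as a main fit followed by a sensitivity fit.

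It is also fair that the charts are aggregate, depend on practice permission and are meant for trial management. The Data collection section gives access to the core team, and the randomisation section lists the statistician separately from that team. However, the informatics section speaks of the research team more broadly, and nothing keeps those who write the plan away from the charts.

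Some stronger readings are tempting, but the documents do not support them:

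- *That the type I error is inflated by a calculable amount.* This would require someone to fit several competing patient-level models and report the most favourable. Aggregate charts yield no such test statistics, and the number of models and their correlation would both be invented.
- *That protection against analyst bias is gone.* Most of the primary analysis is fixed in print.
- *That even the model family is undecided.* The choice between mixed and multi-level models is worded in the practice-level section, which is secondary, and the terms are near-synonyms there. The primary analysis is specified as a non-linear mixed model.
- *That the plan was written late.* Data lock is an outer limit, and the article does not show when the plan was written.
- *That the exposure has a known upper limit.* The wait of up to a year under Anticipated challenges runs from consent and is not the span of start dates. Only the 84-week minimum follows from the schedule.

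**Conclusion.** The point holds in a limited form. The article puts pre-specification in the place of analyst blinding and then sets a deadline that does not guarantee it, because the aggregate before/after outcome is open to the research team for at least 84 weeks before that deadline falls. The choices exposed are three: the coding and scale of time, the primary cross-classification fit, and baseline adjustment. The first is the most consequential, since the candidate models adjust for time in different ways. No numerical bias can be attached to this.

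The conclusion assumes forty practices, no gaps in the start schedule (so 84 weeks is a minimum), and that the team's run charts are the same before-and-after charts the tool shows to practices. The tool's description makes this last assumption the natural reading.

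**What to change.** In the Patient level analysis section, replace the data-lock deadline with a requirement that the analysis plan be signed and dated before the first practice starts the intervention, or at the latest before anyone writing it sees post-start charts. The plan should name one primary model: the scale and form of the time term, the cross-classification fit that counts as primary, and the baseline covariates, if any. Changes after that date should be dated and treated as exploratory under the rule already in the Blinding section.

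The team's access to run charts can stay as it is. Confining the team to activity data would conflict with the prescribing reports in Table 8, and it is unnecessary once the plan is dated early.

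The cost is earlier drafting of a document already promised. No data collection, sample size or intervention delivery changes.

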## Discussion

Although IT-based interventions that identify and target patients with high-risk prescribing for review have previously shown to be potentially effective, there is a need for approaches that are more economically sustainable and produce longer-term effects. The DQIP intervention makes use of the existing NHS IT-infrastructure to continuously identify patients with high-risk prescribing and is targeted at existing practice teams rather than relying on additional professional time/resource, which has obvious advantages, especially in the current financial climate.

### Assumptions underlying the design of the DQIP intervention

The design of the DQIP intervention is based on the assumption that in order to be effective in reducing high-risk prescribing of NSAIDs and antiplatelets, then:

The intervention has to be adopted by practices. Adoption is the process by which clinicians and practices are persuaded that the change promoted by the intervention is worth pursuing, that the intervention itself is likely to lead to benefit, and to then ensure that the intervention is implemented. The DQIP intervention aims to support adoption by providing education, an initial fixed payment of 350 GBP (560 USD; 403 EUR), and email reminders to those practices with minimal use of the DQIP tool.

Practices have to reach patients. A necessary condition for the intervention to work is that it is actually delivered to the right patients at the right time. This requires practices to identify suitable patients to deliver the intervention to. If reach is low, then few patients will receive the intervention, and overall effectiveness will also be low irrespective of how 'effective' the intervention is in patients who actually receive it. The DQIP intervention aims to support reach by timely and continuous identification of patients affected by high-risk prescribing, by email -reminders to practices to review their data, and by offering payment of 15 GBP (24 USD; 17 EUR) per patient reviewed.

Practices have to deliver the intervention effectively to patients who are reached. In DQIP, this implies that the way of reviewing and making decisions about high-risk prescribing have to be plausibly effective in reducing the likelihood of adverse drug events from NSAIDs and antiplatelets. The DQIP intervention aims to support effective delivery by structuring clinical information to facilitate review and by alerting practitioners to situations, where patients are re-prescribed high-risk medication against previously documented intentions.

Practices have to maintain these processes for the duration of the trial. A feature of the PINCER study was that 12-month impact of a one-off pharmacy led review was smaller than the six-month effect [20]. In other words, the intervention effect was not fully maintained, either because new patients were prescribed the targeted drugs, or because patients restarted them, or both. Long-term effectiveness requires that the intervention is maintained. The DQIP intervention aims to support maintenance by continuous (rather than one-off) identification of patients affected by high-risk prescribing over the whole duration of the trial, by monitoring whether any improvements in high-risk prescribing are maintained over time (run chart) and alerting practices if this is not the case, and by payment of 15 GBP (24 USD; 17 EUR) per patient reviewed (rather than one-off).

### Design of outcome measures

The DQIP intervention is designed to change prescribing behaviour in primary care and thus, our primary outcome measure and the majority of secondary outcome measures are designed to reflect such behaviour changes.

The core of the intervention is to review existing high-risk prescribing, but we are also hypothesising a reduction in 'new' prescribing, via the triggering of internal practice processes similar to those that appear to have happened with QOF, where stimulating internal monitoring/surveillance have been important mediators of change [21-24]. We do not have any direct control over these internal processes, but will explore their impact by measuring both change in existing prescribing (patients who have received a targeted high-risk prescription in the previous 12 months) and change in 'new' prescribing (patients receiving a targeted high-risk prescription who have not received one in the previous 12 months).

Although not a primary outcome in this trial, the ultimate aim of changing practitioner behaviour is to improve outcomes for patients. However, prescribing is only one among other healthcare process that (in addition to patients' underlying risk factors) may influence outcomes, which implies that interventions focussing on medication use only are unlikely to significantly alter overall mortality or hospital admission rates. Nevertheless, such outcome measures have been used in a number of trials seeking to assess the impact of medication review interventions [25]. We have therefore designed measures that may more specifically capture the potential impact of the DQIP intervention on patient outcomes, i.e., NSAID and antiplatelet specific hospital admissions that are preceded by high-risk prescribing of these agents (AO 1 to 3). Because state-of-the-art assessment of causality and preventability of adverse drug events over the duration of a trial is usually not feasible (clinical judgement by two or more independent experts is usually required), the outcome measures of the type used here may inform the design of similar trials of interventions seeking to improve and measure changes in drug therapy outcomes.

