### Sample size

In the pilot practices that targeted high-risk NSAID and antiplatelet prescribing, there was a 40% reduction in this prescribing after one round of feedback and review. This is similar to the short-term reduction in high-risk prescribing achieved in the recently completed PINCER trial [16]. We therefore consider a 20% reduction in high-risk prescribing as measured by our outcome measures plausible (and relatively conservative), and have used this in the power calculation. Power calculations for stepped wedge trials are relatively complex, and three estimates are presented.

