**Specific hospital admissions that were preceded by high-risk prescribing**		
AO-1	Patient time with GI risk factors as defined in PO- measures 1 to 6 (Table 4) #	Number of denominator patients admitted with GI bleeding who had any high risk prescription as defined in PO-measures 1 to 6 (Table 4) in the eight weeks before admission
AO-2	Patient time with heart failure as defined in PO-measure 7 (Table 4) #	Number of denominator patients admitted to hospital for HF - exacerbation who had a high-risk prescription as defined in PO-measure 7 (Table 4) in the eight weeks before admission
AO-3	Patient time with renal risk factors as defined in PO-measures 8 to 9 (Table 4)^#^	Number of denominator patients admitted to hospital for acute renal failure or with dehydration or diarrhoea (both defined as potentially inappropriate/ambulatory care sensitive admissions) who had any high-risk prescription as defined in PO-measures 8 to 9 (Table 4) in the eight weeks before admission

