**Specific hospital admissions irrespective of high-risk prescribing**		
AO-4	Patient time with GI risk factors as defined in PO-measures 1 to 6 (Table 4)^#^	Number of denominator patients, who are admitted to hospital for GI bleeding
AO-5	Patient time with heart failure as defined in PO-measure 7 (Table 4)^#^	Number of denominator patients, who are admitted to hospital for HF - exacerbation
AO-6	Patient time with renal risk factors as defined in PO-measures 8 to 9 (Table 4)^#^	Number of denominator patients, who are admitted to hospital for acute renal failure or with dehydration or diarrhoea (both defined as potentially inappropriate/ambulatory care sensitive admissions)

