**Any cause hospital admissions**		
AO-7	Patient time with GI risk factors as defined in PO-measures 1 to 6 (Table 4)^#^	Number of denominator patients admitted to hospital with any emergency admission
AO-8	Patient time with heart failure as defined in PO-measure 7 (Table 4)^#^	Number of denominator patients admitted to hospital with any emergency admission
AO-9	Patient time with renal risk factors as defined in PO-measures 8 to 9 (Table 4)^#^	Number of denominator patients admitted to hospital with any emergency admission

^# ^The denominator is the time that each patient is defined as having risk factors by virtue of age, disease or co-prescribing in the year before the intervention and the year of follow-up. AO measures 1 to 3 consider specific hospital admissions where patient has had a recent high-risk prescription; AO measures 4 to 6 consider specific hospital admissions irrespective of whether or not the patient has a had a recent high-risk prescription; AO measures 7 to 9 consider all emergency admissions

**Table 7 T7:** Measures of wider impact on NSAID prescribing (VO = Volume outcomes)

VO-1	Total NSAID prescription volume/registered patients in participating compared to non-participating practices
VO-2	Proportion of patients prescribed an NSAID stratified by age in participating compared to non-participating practices

**Key: **NSAID = Non-steroidal anti-inflammatory drug

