### Cost-effectiveness

The cost-effectiveness of the intervention will be measured as the cost per reduction in high-risk prescribing and cost per reductions in hospitalisations from an NHS perspective.

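### AO-1 to AO-3 count an admission only if the targeted prescription preceded it, so less prescribing is expected to lower them even when no admission is prevented

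*Protocol article*

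**What the plan says.** Table 6 of the protocol article defines nine admissions outcomes in three groups.

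- **AO-1 to AO-3** need both an admission and a targeted prescription in the eight weeks before it. AO-1 reads "Number of denominator patients admitted with GI bleeding who had any high risk prescription as defined in PO-measures 1 to 6". AO-2 counts patients "admitted to hospital for HF - exacerbation who had a high-risk prescription as defined in PO-measure 7". AO-3 counts renal failure, dehydration or diarrhoea admissions in patients "who had any high-risk prescription as defined in PO-measures 8 to 9".
- **AO-4 to AO-6** count the same types of admission without the prescription condition. AO-4 is "Number of denominator patients, who are admitted to hospital for GI bleeding".
- **AO-7 to AO-9** count any emergency admission.

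The footnote gives all nine the same kind of denominator: "The denominator is the time that each patient is defined as having risk factors by virtue of age, disease or co-prescribing". It is time at risk, whether or not a high-risk prescription was in force.

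The Discussion (Design of outcome measures) picks out AO-1 to AO-3 as "measures that may more specifically capture the potential impact of the DQIP intervention on patient outcomes". It does not say that a change in prescribing enters their numerators by definition.

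Two other places matter. The Sample size section says "We therefore consider a 20% reduction in high-risk prescribing as measured by our outcome measures plausible", and Table 1 expresses this as 10% to 8%. The Cost-effectiveness section plans a "cost per reductions in hospitalisations from an NHS perspective" without naming the admissions measure to be used.

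**The concern.** With this numerator and denominator, the AO-1 rate is the share of at-risk time under high-risk prescription multiplied by the admission rate among those exposed. The intervention is meant to reduce the first factor, which is essentially what the prescribing outcomes already measure. A patient whose high-risk prescription ends and who is later admitted anyway drops out of AO-1, yet nothing was prevented. For AO-1 there is a second route. Measures PO-1 to PO-6 count a prescription as high-risk only when no gastro-protective drug accompanies it, so adding one also removes any later bleed from the count, even though the bleed occurred.

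AO-1 to AO-3 therefore cannot separate admissions prevented from admissions reclassified. If they are read as the more specific evidence of patient impact, a success on the prescribing outcome could be reported a second time as fewer drug-related admissions.

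**Working it through.** The plan states no expected figure for AO-1 to AO-3, so there is none to reproduce. The one planning figure used is the fall in high-risk prescribing: Table 1 gives 10% to 8%, and (10 - 8)/10 = 20%, which agrees with the Sample size section.

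**Inputs**
- Share of at-risk time exposed: p0 = 0.10 before and p1 = 0.08 after (Table 1). These are used for illustration; the document does not give the share for the GI, heart failure or renal groups separately.
- Causal RR of admission under high-risk prescription: not in the document. Assumed 1, 1.5, 2 and 3.
- Admission rate when unexposed: not in the document. Assumed r0 = 5 per 1000 patient-years. It cancels from every percentage and ratio below.
- Patients whose high-risk prescribing stops have the average admission risk of the exposed, and return to r0 afterwards (assumption, varied below).

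**Formulas**
- AO-1 rate = p × RR × r0
- AO-4 rate = p × RR × r0 + (1 - p) × r0 = r0 × [1 + p(RR - 1)]
- Relative change in AO-1 = p1/p0 - 1 = 0.08/0.10 - 1 = -20%, with no RR in it
- Relative change in AO-4 = [1 + 0.08(RR - 1)]/[1 + 0.10(RR - 1)] - 1
- Absolute fall in AO-1 = 0.02 × RR × r0; in AO-4 = 0.02 × (RR - 1) × r0; their ratio = RR/(RR - 1)

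**Results (rates per 1000 patient-years)**

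| RR | AO-1 before → after | Change | AO-4 before → after | Change | Absolute fall, AO-1 vs AO-4 | Ratio |
|---|---|---|---|---|---|---|
| 1 | 0.50 → 0.40 | -20% | 5.00 → 5.00 | 0% | 0.10 vs 0 | unbounded |
| 1.5 | 0.75 → 0.60 | -20% | 5.25 → 5.20 | -0.95% | 0.15 vs 0.05 | 3.0 |
| 2 | 1.00 → 0.80 | -20% | 5.50 → 5.40 | -1.8% | 0.20 vs 0.10 | 2.0 |
| 3 | 1.50 → 1.20 | -20% | 6.00 → 5.80 | -3.3% | 0.30 vs 0.20 | 1.5 |

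The AO-1 percentage is the same whether the drugs cause none of the admissions or many of them. AO-4 does distinguish these cases.

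**Sensitivity of the 20%**
- If patients who stop carry k times the average exposed risk, AO-1 falls by 0.02k/0.10: 10% at k = 0.5, 5% at k = 0.25, and nothing at k = 0.
- Some targeted drugs, such as aspirin or warfarin, also define the at-risk group. If every patient who stops leaves the denominator too, the change is (0.08/0.98)/0.10 - 1 = -18.4%.

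The size of the fall depends on who stops, but a fall is expected unless those patients have no admission risk at all.

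**Would a rate per exposed time do better?** No. AO-1 divided by p is RR × r0 both before and after, so it does not move with the intervention at any RR.

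**The case against.** The strongest reply is that the plan already holds the safeguard. AO-4 to AO-6 count the same admissions without the condition, on the same denominators; the Table 6 footnote spells out the difference; and all nine measures are planned secondary outcomes, so readers will see both sets. The Discussion is also cautious. It says admissions are not a primary outcome, that medication-only interventions are unlikely to shift overall admission rates, and that formal causality assessment is usually not feasible. It nowhere claims that AO-1 to AO-3 are independent proof of benefit. All of this stands and lowers the severity. It does not cure the point: the text singles out the set that moves by construction and does not say it must be read against AO-4 to AO-6.

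A reader might go further in three ways that the document does not support.

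- *That AO-1 overstates benefit at least sixfold.* This divides a 20% fall by a 3.3% fall, two percentages on very different bases, and it depends on stopping at RR 3 (at RR 4 the AO-4 change is -4.6%, and 20/4.6 is about 4.3). For admissions avoided the absolute scale is the relevant one, and there the ratio is RR/(RR - 1).
- *That AO-1 to AO-3 must fall whenever prescribing falls, so a positive result is almost automatic.* The full proportional fall needs patients who stop to have average exposed risk. The document gives no admission rates, so whether a fall in such narrowly defined events would be detectable is unknown.
- *That the economic evaluation will cost AO-1 to AO-3 admissions.* The Cost-effectiveness section does not say which hospitalisations it uses, and an article may leave that detail to the full protocol. The concern applies there only if AO-1 to AO-3 were intended.

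**Conclusion.** The point holds as a defect in how three secondary outcomes are defined and read. The definitions in Table 6 are enough to establish it; only its size needs assumptions. Those are the Table 1 exposure figures, average risk among patients who stop, and RRs that the document does not supply. On them, the planned 20% fall in prescribing yields a 20% fall in AO-1 even if total GI-bleed admissions do not change, and for RR 1.5 to 3 the number of admissions apparently avoided is 3.0 to 1.5 times the true number. AO-2 and AO-3 have the same structure and behave in the same way. The primary outcome and AO-4 to AO-9 are not affected.

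**What to change.** - In the Discussion (Design of outcome measures), state that any claim of patient benefit from fewer admissions rests on AO-4 to AO-6.
- Label AO-1 to AO-3 as descriptive and partly determined by the prescribing outcome, and say that a fall in them alone does not show that admissions were prevented.
- If AO-1 to AO-3 were meant to feed the cost per reduction in hospitalisations, use AO-4 to AO-6 there instead, and name them.

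This is a change of wording only; AO-4 to AO-6 are already planned and no new data are needed. The cost is in what can be claimed. AO-4 to AO-6 are diluted by admissions in unexposed patients, with expected changes of only 0% to about 3% in the illustration above, so the admissions statement will be more modest and may be inconclusive.
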